### Randomization

Randomization will be performed by means of the minimization method using Minim randomization software, which is a biased-coin approach with a probability of 0.7 to 0.8 for allocation of the “best fitting” treatment [36]. The minimization method obtains an overall balanced distribution of participants, as the number of expected participants is too small for true randomization. Furthermore, participants will be randomized at each site in order to obtain an equal distribution within each municipality/treatment center. This approach was chosen to (a) reduce the impact of geographical variation between the treatment conditions and (b) reduce the risk of counselors not being able to conduct the treatment type to which they were allocated [37]. The following variables will be used for randomization, all based on patient report:
sexage (dummy coded as 0 if age < 40 years, 1 if age ≥ 40 years).duration of current OAT treatment (four categories: 0–3 months, 4–5 months, 6–12 months, ≥12 months).days of injection drug use in the past month (dummy coded as 0 if 0–9 days, 1 if ≥10).having been employed or studying at least three of the past 6 months.having received a psychiatric diagnosis from a psychiatrist.

After entering the data for an anonymous new patient into a central database, the referring clinician will contact the Center for Alcohol and Drug Research on a telephone number devised for this purpose and will receive a response to randomization.

At the first counselling session after study enrollment, all participants will be assessed using the YouthMap assessment form [38] or the AdultMap assessment form, depending on the age of the participant. The YouthMap and AdultMap assessment forms are comprehensive assessment tools tailored for people in treatment for psychoactive substance use disorders. The AdultMap is almost identical to the YouthMap, with the exception of a few additional items related to any children in the respondent’s care, as well as fewer items related to education. The follow-up assessments will be conducted via telephone interviews at three and nine months post-randomization. The time plan for the study is shown in Table 1 in Appendix.

#### Data management

Quantitative data will be entered into a secure server located in Denmark and run by SurveyXact. The Centre for Alcohol and Drug Research, Aarhus University will design, set up, and host the database. At the end of the trial, all data will be uploaded to a server at Statistics Denmark in order to allow merging with national registers.

#### Statistical analyses

Quantitative data analyses will be performed in STATA V16.0. All descriptive analyses, including the recruitment rate, dropouts, losses to follow-up, and the prevalence of serious adverse events will be reported post-randomization and summarized by treatment arm. All causes of withdrawal from randomized treatment will be reported. All of this information will be provided in the form of a CONSORT flowchart (see Fig. 1).

**Fig. 1 Fig1:**
[figure not shown]
CONSORT Flowchart

Summaries will be presented as means and standard deviations for variables that are approximately normally distributed, or as medians and interquartile ranges for skewed variables. Categorical variables will be summarized as frequencies and percentages. Transformations will be used when distributional assumptions are not fulfilled for inferential tests on a continuous measure. We will examine and account for the influence of clustering at the site level on the outcomes. All models will adjust for stratification factors and randomized treatment.

The primary analysis will be an intention-to-treat analysis, utilizing all available data from all randomized participants. Retention in OAT will be compared between the two conditions, controlling for sex, age, and time in treatment, using Cox proportional hazards regression. All randomized participants will be analyzed within the treatment arm to which they were originally allocated after randomization, regardless of whether they retained that specific treatment over the course of the trial or not.

Random intercepts will be estimated for site using the shared option in Stata 16. The primary outcome will be analyzed 365 days after the last patient has been randomized, in order to allow sufficient time for dropouts to occur. Secondary outcome analyses will be performed similarly, controlling for baseline values. For sessions attended, a generalized structural equation model will be estimated specifying a Poisson outcome. For severity of drug use, we will estimate a linear regression model with random intercepts for individual patients and sites. This model will control for age and sex and include the interaction between randomization status (ILC versus standard) and assessment wave (baseline, three, or six months).

For number of convictions, we will assess a Poisson, negative binomial, or Poisson or binomial analysis with zero-inflation. The best-fitting model will be selected based on the Bayesian information criterion [39], without regard to the coefficients or which model favors ILC. We will explore the impact of non-engagement with the intervention and loss to follow-up for secondary variables by undertaking exploratory complier adjusted analyses [40]. No interim analyses or formal subgroup analyses are planned.

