### Outcomes

The primary outcome measure is retention in OAT. Retention in treatment will be calculated starting on the date of randomization and until the patient is discharged or the trial ends. Patients who are registered as having completed a successful course of treatment will be considered censored at the date of discharge, as was the case in the pilot trial [23]. Any reason for discharge, other than completed treatment, will be considered dropout, even if discharge is on patient request. In general, discharge occurs when the patient no longer receive any services. Note that practices may vary slightly between sites in terms of their practices when discharging patients. As researchers we are legally and practically unable to influence these decisions. None of the participating sites discontinue OAT against patients’ wishes, neither because of substance use, nor because of failure to attend treatment. Only the present episode is considered in this trial (i.e., the episode that is initiated or ongoing at the time of randomization).

The secondary outcomes are 1) substance use other than prescribed medications (AdultMAP) [1]; 2) self-reported days in the last month with offences for profit (AdultMAP); 3) substance use and everyday functioning (concentration, planning, keeping appointments, sleeping, eating habits, cleaning etc.) in the last month (AdultMap) and last week (WOM); 4) social interaction with individuals (family, friends, acquaintances) with non-criminal behavior and/or with no substance abuse in the last month (AdultMap); 5) employment/educational activities in the last month (AdultMap).

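### The named primary Cox model adjusts for three of the six minimisation factors, although the plan says every model adjusts for the stratification factors

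*Protocol article*

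**What the plan says.** The Randomization section of the protocol article describes minimisation by biased coin, carried out within each of four sites. Six patient-reported variables are used: sex, age (split at 40), OAT duration ("duration of current OAT treatment (four categories"), injection days in the past month (under 10, or 10 and more), employment ("having been employed or studying at least three of the past 6 months"), and a psychiatric diagnosis.

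The Statistical analyses section, in the text below Fig. 1, makes four statements on adjustment:

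- A general rule: "All models will adjust for stratification factors and randomized treatment".
- The primary model: "Retention in OAT will be compared between the two conditions, controlling for sex, age, and time in treatment, using Cox proportional hazards regression".
- Site: "Random intercepts will be estimated for site using the shared option in Stata 16".
- The drug-use model: "This model will control for age and sex", together with random intercepts for patients and sites and an arm-by-wave interaction.

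The term stratification factors is not defined. No reason is given for leaving out injection days, employment or study, and psychiatric diagnosis.

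**The concern.** The rule and the named model do not agree. An analyst who follows the rule, taking the allocation variables as the stratification factors, fits six factors. One who follows the model sentence fits three. Both could say that they kept to the plan. Participants and clinicians are not blinded, so the covariate list of the primary test should not stay open until outcomes are known.

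There is also a loss of information. The three omitted factors are recorded before allocation for every patient, and they were presumably chosen because they were thought to matter for outcome. The hazard ratio is non-collapsible: if a prognostic factor is left out, the estimate moves towards 1 relative to the effect conditional on that factor, and power tends to fall.

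**Working it through.** **1. Factor count.** Allocation uses six factors plus site. The primary model has sex, age and time in treatment (taken to be OAT duration), plus a site frailty. Omitted: 6 − 3 = 3. The drug-use model has two factors plus site. Omitted: 6 − 2 = 4.

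**2. The plan's own figure.** The Sample size section gives 137 for a hazard ratio of 0.62, 80% power and alpha 0.05. The Schoenfeld formula, two-sided with equal arms, gives 4 × (1.960 + 0.842)² / (ln 0.62)² = 4 × 7.849 / 0.2285 = 137.4, so the figure is reproduced. The formula takes no covariates, so this point does not change it. It counts events, however, and events will be fewer than 137 unless every patient drops out. That matters for step 4.

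**3. Size of the effect, by simulation.** The documents give no prognostic effects, site variation or dropout rate, so these are assumptions. Settings: 137 patients; four sites holding 40, 25, 20 and 15% of them; biased coin 0.75 within site; site standard deviation 0.4 on the log-hazard; 76 to 95 events on average. Each omitted factor had a log hazard ratio of ±0.3 (weak) or ±0.7 (strong). OAT duration was entered as one indicator. There were 2,500 trials per scenario.

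| Omitted factors | Model | Mean HR (true 0.62) | Power | Type I error |
|---|---|---|---|---|
| Weak | 3 factors, shared frailty (as planned) | 0.618 | 52.4% | 5.2% |
| Weak | 3 factors, site strata | 0.615 | 51.9% | 4.9% |
| Weak | 6 factors, site strata | 0.604 | 54.1% | 5.3% |
| Strong | 3 factors, shared frailty (as planned) | 0.646 | 50.8% | 5.0% |
| Strong | 3 factors, site strata | 0.644 | 50.4% | 4.7% |
| Strong | 6 factors, site strata | 0.603 | 59.0% | 5.7% |

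Gain over the planned model: 54.1 − 52.4 = 1.7 points (weak) and 59.0 − 50.8 = 8.2 points (strong). With site strata in both models: 54.1 − 51.9 = 2.2 and 59.0 − 50.4 = 8.6 points. Six factors with shared frailty was not fitted. The near-equality of frailty and strata with three factors is the reason to expect a similar gain.

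The Monte Carlo standard error of a 5% rate is √(0.05 × 0.95 / 2500) = 0.44 points. The planned model's 5.2% and 5.0% are at the nominal level. The six-factor 5.7% lies 0.7 / 0.44 = 1.6 standard errors above it.

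A smaller simulation used a lower event share (about 34%) and omitted-factor hazard ratios of 1.8, 0.55 and 1.65. With site strata in both models, power was 34.2% with three factors and 37.8% with six, a gain of 3.6 points. With 500 runs the unpaired standard error of that difference is √(0.342 × 0.658 / 500 + 0.378 × 0.622 / 500) = 3.0 points. The direction agrees, but the figure is imprecise.

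**4. Cost in parameters.** At an assumed 34% dropout, events are 0.34 × 137 ≈ 47. With OAT duration in four categories, the six-factor model has 1 + 1 + 1 + 3 + 1 + 1 + 1 = 9 coefficients, or 47 / 9 ≈ 5 events each. With duration as a trend it has 7, or 47 / 7 ≈ 7 each.

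**The case against.** The contradiction can be softened. The article never calls the six variables strata, and the only stratum-like element is allocation within site, which the frailty covers. The general rule and the named covariates could also be read together, since the article does not say that the three are the only ones. A full covariate list may sit in the analysis plan. These readings are possible, but none explains why the model names exactly three of the six allocation variables. Nor is this a matter of missing detail: the article states both a rule and a list, and they do not match.

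A small covariate set is defensible when events are few. That stands as a reason to limit the parameters, but it should be stated. The estimation gain is also mixed. With weak factors the planned model averaged 0.618, closer to 0.62 than the six-factor model at 0.604. With strong factors the planned model erred towards 1 (0.646) and the six-factor model away from it (0.603). Part of the shift is the difference between two estimands, not bias.

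A reader might infer that a three-factor test after minimisation on six factors is conservative. The simulations do not show this: the planned model's type I error was 5.2% and 5.0%. In the smaller simulation, three-factor models without and with site strata gave 6.8% and 5.0% in 400 runs, where the standard error is about 1.1 points.

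A reader might also infer that a frailty variance estimated from four sites disqualifies the site term, particularly as "practices may vary slightly between sites in terms of their practices when discharging patients". The variance is poorly estimated: it came out near zero in 27 to 30% of simulated trials. Yet frailty and strata differed by at most 0.5 points in power and 0.3 points in type I error. These trials gave all sites the same hazard shape, so they do not test differing shapes. Shared frailty is nonetheless an accepted method, and the article speaks only of slight variation.

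**Conclusion.** The point holds as an inconsistency in the specification of the primary analysis. The plan's adjustment rule and its named Cox model disagree, and three of the six allocation factors are left out without a reason. The drug-use model departs further from the rule.

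The size is modest and conditional. Power falls by about 2 points if the omitted factors are weak and about 8 if they are strong. Attenuation appears only in the strong case. These figures rest on assumed prevalences, effects, site variation and event rates. The validity of the test is not in question, and the required number of events does not change. The documents do not support replacing the shared frailty. The change is worth making because it settles which model is primary, at the price of a wording edit.

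**What to change.** Define stratification factors, and name one primary Cox model before outcome data are examined: arm, sex, age, OAT duration, injection days (<10 / ≥10), employment or study, and psychiatric diagnosis, with shared frailty for site as planned. Add a Cox model stratified by site as a sensitivity analysis. Use the same factor list in the secondary models, including the drug-use model, alongside the baseline values already planned. If the sponsor prefers three factors, the general rule should be rewritten to say so, with the reason.

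The change needs no new data, since all six variables are collected for allocation. The cost is three more parameters in the primary model, which could strain it if dropout is low, and the six-factor type I error in simulation was slightly above nominal (5.3% and 5.7%). Entering OAT duration as a single trend term removes two coefficients; that choice should also be made in advance.

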Compared with patients with other substance use disorders, people with opioid use disorders have the highest risk of criminal activity, psychiatric comorbidity, poly-substance use, infections, such as HIV and hepatitis C [10, 11], as well as excess mortality [12, 13] and a high degree of somatic comorbidity [14]. However, this is primarily due to the fact that opioid use disorders represent the most severe end of the substance use disorder spectrum, and while opioid use disorder is associated with antisocial personality traits, this is mostly as part of its overall relationship with a general propensity for substance use disorders [15]. Once opioid use disorder is established, however, criminal offending may be reduced by the provision of medication assisted treatment [16].

The dual burden of using a drug with particularly heavy consequences and externalizing behavior problems may put some patients at very high risk for a range of adverse outcomes. A considerable barrier to benefitting from treatment is staying in contact with the system for a sufficient time; around 30% of patients drop out of psychosocial treatment across types of substances and treatment, and dropout rates are even higher for more disadvantaged patients and treatments that demand time and concentration [17, 18]. Furthermore, a growing body of evidence suggests that patients with externalizing and criminal behavior are particularly hard to retain in treatment and offer relevant help but that improved retention and treatment effects may be associated with substantially lower costs of crime [19, 20]. Thus, improving retention and outcomes for people with externalizing disorders who enroll in OAT is of crucial importance.

One way to improve retention and outcomes is the use of contingency management (CM) in the form of voucher-based reinforcement therapy [21]. However, the evidence base for specially tailored programs to serve the needs of people with opioid use disorder who are high on externalizing problems is extremely limited. A recent narrative review based on a small handful of studies indicated that cognitive behavioral therapy and CM, or milieu therapy alone or in combination with other interventions, have not been differentially effective for patients with opioid use disorder and antisocial personality disorder [22].

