### Eligibility criteria

Inclusion criteria are as follows: 1) seeking or currently receiving treatment for opioid use disorder at one of the participating sites; 2) over 18 years of age; 3) able to attend the evaluation and treatment sessions 4) score of three or above on the YouthMap12 Externalizing difficulties subscale [1].

Patients will be excluded if they have a severe mental disorder (e.g. current psychosis), cognitive difficulties, or severe aggressive and chaotic behavior that would preclude their participation in the counselling sessions.

Social workers and/or nurses at each participating site will assess whether an individual is eligible for study participation according to the eligibility criteria during the first in-person contact with the participating treatment sites, or among the patients already enrolled in OAT at the sites. If the individual is deemed eligible, the same employee will inform the individual about the trial verbally, and provide a participant information sheet. If the individual gives informed consent for study participation, the employee will collect the necessary information for randomization in an online questionnaire, which will be forwarded to the Centre for Alcohol and Drug Research, Aarhus University via an anonymous and secure email. The research team will ensure the confidentiality of this data by keeping the online questionnaire data and consent forms stored on secured servers. After randomization, the study participant will be assigned to one of the two treatment conditions that are tested in the study. Participants and clinicians cannot be blinded to the conditions that the participants will be randomized to, but the persons who will conduct the assessments at the follow-ups will be blinded.

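### The primary Cox model does not use the YouthMap12 externalizing score, an entry measure known before randomization; this forgoes possible precision and power but does not invalidate the test

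*Protocol article*

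**What the plan says.** **Primary model.** The Statistical analyses section of the protocol article names three covariates: "Retention in OAT will be compared between the two conditions, controlling for sex, age, and time in treatment, using Cox proportional hazards regression". The same section adds a general rule, "All models will adjust for stratification factors and randomized treatment", and a site term: "Random intercepts will be estimated for site using the shared option in Stata 16".

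**Allocation.** The Randomization section introduces its list with "The following variables will be used for randomization, all based on patient report". The list is sex, age (below 40 or not), duration of current OAT in four categories, injecting days, employment or study, and psychiatric diagnosis. Minimization is done within site. The externalizing score is not listed.

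**The score.** Eligibility criteria requires a "score of three or above on the YouthMap12 Externalizing difficulties subscale". Site staff "assess whether an individual is eligible for study participation according to the eligibility criteria during the first in-person contact", or among patients already enrolled in OAT. This comes before consent and allocation.

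**Prognosis.** The Background says that "patients with externalizing and criminal behavior are particularly hard to retain in treatment". It also associates externalizing psychopathology with dropout from substance use treatment. It then qualifies this: the relationship varies widely and may appear mainly when the patient gains little from treatment beyond their own wish to change.

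**The concern.** The score is the entry criterion that measures the trait ILC is meant to address. It should exist for every randomized patient, and it predates allocation. The fuller YouthMap or AdultMap assessment, by contrast, takes place at the first counselling session after enrolment. The Background gives this trait a reason to predict retention and gives none for sex or age, which are in the model.

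If the score predicts dropout among those enrolled, a Cox model without it has less power and a hazard ratio nearer 1 than a model with it. Any chance difference between arms on the score also stays in the estimate as noise. The choice should be made in advance, because a covariate added after an imbalance has been seen looks data-driven.

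**Working it through.** **1. Is the score brought in indirectly?** The named list (sex, age, time in treatment) is shorter than the minimization list, and the all-models rule does not say which governs; the two sentences need reconciling. The score is absent on either reading.

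**2. Reproduce the plan's figure.** Sample size gives a hazard ratio of 0.62, 80% power, alpha 0.05 and a total of 137. Schoenfeld's formula, two-sided, 1:1:

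d = 4(1.960 + 0.842)² / (ln 0.62)² = 31.40 / 0.2285 = 137.4

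Power with 137 events is 79.9%. So 137 reproduces, but as a number of events.

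**3. Power without and with the score.** Assumed, because the article does not give them: the score's hazard ratio per SD and the share of patients with an event. The Background's dropout figure of around 30% concerns psychosocial treatment in general, not OAT retention. All runs use 137 patients, exponential times, a treatment hazard ratio of 0.62 and a normally distributed score as the only covariate.

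*Setting A: fixed event share, 2,000 runs per cell. Power in %, without → with the score.*

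| HR per SD | 30% (41 events) | 60% (82 events) | 100% (137 events) |
|---|---|---|---|
| 1.0 | 30.5 → 30.7 | 57.8 → 58.0 | 79.7 → 79.9 |
| 1.2 | 30.4 → 31.1 | 54.6 → 56.0 | 76.4 → 78.4 |
| 1.5 | 31.2 → 31.7 | 53.2 → 58.7 | 66.2 → 76.7 |
| 2.0 | 26.3 → 30.7 | 44.6 → 57.9 | 53.6 → 77.8 |

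*Setting B: accrual over 1.5 years plus at least 1 year of follow-up, 800 runs per cell. Columns give 12-month dropout in the control arm.*

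| HR per SD | 30% (about 54 events) | 60% (about 95 events) |
|---|---|---|
| 1.2 | 41.4 → 41.9 | 63.8 → 65.0 |
| 1.4 | 38.1 → 40.1 | 60.1 → 64.1 |
| 1.7 | 34.5 → 40.6 | 52.2 → 62.0 |

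Gains are 0.2 to 2.0 points up to 1.2 per SD, and 0.5 to 10.5 points from 1.4 to 1.7. At 2.0 they are about 4 to 24 points. At 1.0, where the score predicts nothing, no power is measurably lost.

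**4. Validity.** With no treatment effect, Setting A rejected in 3.8% to 6.1% of runs without the score and 4.1% to 6.2% with it. Both are close to 5%.

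**5. Chance imbalance.** In Setting B the difference between unadjusted and adjusted log hazard ratios had an SD of 0.04 to 0.10. The standard error of the log hazard ratio is about 2/√54 = 0.27 with 54 events and 2/√95 = 0.21 with 95. The shift is smaller than the standard error and already part of it.

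**6. Cost in parameters.** Treatment (1), sex (1), age (1), OAT duration (3), injecting (1), employment or study (1) and psychiatric diagnosis (1) make 9. With 54 events that is 54/9 = 6.0 events per parameter, and 54/10 = 5.4 with the score added.

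**The case against.** A short prespecified covariate list is legitimate, and nothing in the article promises adjustment for this score. The Background describes patients with externalizing behavior as a group. It shows no gradient among those already scoring three or above, and cutting the range at entry tends to weaken any association. The outcome is retention in OAT, and the Outcomes section says that no site ends OAT against the patient's wishes. Injecting, employment and psychiatric diagnosis may already carry part of what the score predicts, and the simulations had no other covariates. With few events another term is not free. All of this stands, and it makes the lower part of the range plausible.

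It does not remove the point. The article fixes a named list for its primary test, so the choice was not simply left to a later document, and adding the score cost nothing measurable in simulation even when it was uninformative.

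Three stronger readings are tempting but unsupported:

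- *Externalizing severity drives dropout in this trial.* The Background reports a variable association and gives no effect size.
- *Uncorrected imbalance distorts the result.* A shift SD of 0.10 would move 0.62 to between 0.51 and 0.75 at the 95% limits (0.62 × e^±0.196). That looks alarming alone, but with 54 events the ordinary 95% interval is already about 0.36 to 1.06 (0.62 × e^±0.533).
- *Variation above three is thrown away.* The article does not say that only pass or fail is kept. It says only that staff enter what randomization needs, and the score is not a randomization variable, so whether the number is kept is unconfirmed.

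**Conclusion.** The point holds as one of efficiency, not validity. A relevant baseline value that should be available for everyone is left out of the primary model, with no bias in the randomized comparison and no inflation of type I error. The likely gain runs from nothing to about 10 points of power, depending on a prognostic strength that the article does not give. The larger gains at 2.0 per SD have no support in it.

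The main power problem lies elsewhere. If 137 is the number of patients, Schoenfeld power at 0.62 is about 65% with 70% events, 51% with 50% and 33% with 30%. Adjustment does not repair that: in Setting A at 60% events, adjusted power is still only 56% to 59%.

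**What to change.** Confirm that the numeric YouthMap12 externalizing score, not only whether the threshold was met, is kept from the eligibility assessment for every randomized patient. Before outcome data by arm are seen, prespecify it as a continuous covariate in the primary Cox model. In the same edit, state one definitive covariate list, so that the named covariates and the stratification-factor rule agree.

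The cost is at most one field in an existing form and one degree of freedom. If events prove few, that term joins a model already carrying the minimization factors, so the full list should be judged against the expected number of events. The reported hazard ratio would then be conditional on the score and should be described so.
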